[name] (SPARKLE Research Assistant). Departments of Psychiatry and Experimental Psychology, University of Oxford ([contact]).

[name] (Junior Trial Health Economist). Department of Health Service and Population Research, Institute of Psychiatry, Psychology & Neuroscience, King’s College London ([[contact]](mailto:[contact])).

[name] (Co-SPACE Research Assistant). Departments of Psychiatry and Experimental Psychology, University of Oxford ([[contact]](mailto:[contact])).

[name] (HCI collaborator). Department of Child & Adolescent Psychiatry, Institute of Psychiatry, Psychology & Neuroscience, King’s College London ([[contact]](mailto:[contact])).

[name] (Co-I). Departments of Psychiatry and Experimental Psychology, University of Oxford ([[contact]](mailto:[contact])).

[name] (PI - corresponding author). Department of Child & Adolescent Psychiatry, Institute of Psychiatry, Psychology & Neuroscience, King’s College London ([[contact]](mailto:[contact])).

1. **b) Name and contact information for the trial sponsor**

King’s College London

Address: [name]

[contact]

Email: [[contact]](mailto:[contact])

1. **c) Role of sponsor in trial design**

The sponsors and funders played no role in the trial design.

1. **d) Trial oversight**

A Trial Steering Committee (TSC) will be convened and will meet approximately every 4 months throughout the study. Recruitment to the trial will be rapid and no interim analyses are planned so a separate Data Monitoring and Ethics Committee (DMC) will not be formed. However, we reserve the option to form one if the TSC deem it necessary at any point during the trial.

**Protocol amendments**

The following changes have been made to the protocol.

| *Version* | *Date* | *Amendment* |
| --- | --- | --- |
|  |  |  |

1. **Introduction**

The COVID-19 related lockdowns and continuing distancing measures have presented families with unprecedented challenges. Extended joint confinement, often within very limited space, isolation from friends and family, increased demands on parents to deliver home-schooling in face of competing work demands, mental health- and money-related worries, all have placed relationships between parents and their children under great pressure. Consistent with this, Co-SPACE, a UK-wide, UKRI and Westminster Foundation-funded cohort study tracking changes in families’ mental health since early lockdown (Waite & Creswell, 2020) found a significant rise in parent-reported children’s behaviour problems and associated family-related stress (Skripkauskaite et al. 2021; Shum et al., 2021). Strikingly, 70% of parents in Co-SPACE reported wanting extra support concerning their child’s response to the pandemic and associated restrictions (Waite, Patalay, Moltrecht, McElroy, & Creswell, 2020).

There is also widespread concern amongst professionals that these problems may increase further as the pandemic continues, and with it, the restrictions put on people’s lives. Families are faced with the continuous need to readjust to new routines, structures and challenges. There is also ongoing disruption to school attendance. Between September and December 2020 many children in the UK were facing periods of repeated isolation due to cases being identified among staff and pupils. Since January 2021 and the introduction of a third national lockdown, schools switched to remote teaching for a second time and for the majority of children parents were again required to supervise remote learning or even deliver home-schooling. These continuous challenges are going to increase pressures on schools (Henshaw, 2020) and already overstretched children’s services (Ford, 2020), as more parents seek additional support and advice from professionals. This will further increase the already substantial gap between provision and need, leaving many families without access to vital support and unresolved difficulties that are more likely to become persistent and impairing. To address this, public health level interventions are needed to support parents in managing common difficulties and stressors. Parenting interventions, based on behavioural and social learning theories, are recommended as the first approach for intervention across a range of child mental health and behavioural difficulties (e.g., National Institute for Health and Care Excellence, 2013).

In SPARKLE, we will examine whether providing families of primary school-aged children within the Co-SPACE cohort with a digital application delivering information and parenting support, *Parent Positive,* can reverse the negative effects of the pandemic on children’s conduct problems while reducing levels of psychological distress in the parents. *Parent Positive* is a digital public health intervention that can be delivered rapidly at scale to support parents in managing their children’s behaviour to reduce conduct problems and levels of family conflict, which were exacerbated during the first lockdown, and which may increase further in future months as families need to cope with continuous uncertainty and further disruption to their daily lives. Co-designed with parents and based on decades of parenting research, *Parent Positive* consists of three elements: (i) *Parenting Boosters:* where advice, delivered in the form of narrated animations, videos, graphics and text is provided to help parents with eight common parenting challenges; (ii) *Parenting Exchange*: a facilitated parent-to-parent communication and peer support platform and; (iii) *Parent Resources:* giving access to carefully selected high-quality, evidence-based online parenting resources. As such, SPARKLE represents one of the first attempts to embed a parenting intervention trial into an ongoing longitudinal cohort study as part of a rapid deployment strategy for intervening to mitigate the negative effects of a national health crisis on families. By doing this, it has potential to provide the evidence base to motivate the national dissemination of *Parent Positive.*

1. **Objectives**

SPARKLE has six aims:

1. To test whether *Parent Positive* reduces the average levels of parent-reported child conduct problems in a self-selected community sample, measured over a one (primary outcome) and two month (secondary outcome) period, when compared to Follow-up As Usual (FAU).
2. To test whether *Parent Positive* reduces the average levels of parent psychological distress, parental child-related stress and worries, family conflict and child emotional problems (additional secondary outcomes) in a self-selected community sample, measured over a one and two month period, when compared to FAU.
3. To assess the extent to which the effects of *Parent Positive* on the primary conduct outcome are moderated by levels of (i) pre-existing levels of conduct problems and (ii) *Parent Positive* usage levels as monitored during the one month intervention period. Usage of *Parent Positive* will be monitored for two months for descriptive purposes.
4. To test the cost-effectiveness of *Parent Positive* compared to FAU over a two month follow-up period.
5. **Exploratory:** To assess whether the effects of *Parent Positive* on primary and secondary outcomes are moderated by baseline characteristics - family social economic status and composition, parental psychological distress, child age, symptoms of attention-deficit/hyperactivity disorder and emotional problems.
6. **Exploratory:** (ii) to explore the impact of lockdown circumstances and policies at baseline on the effects of *Parent Positive* on primary and secondary outcomes. Data on lockdown circumstances will be collected at one and two months post-randomisation for descriptive purposes.

Note that these exploratory aims may not be addressed in the primary trial results paper.

Hypotheses:

1. At both one and two months post-randomisation, *Parent Positive* will reduce the average levels of parent-reported child conduct problems in a self-selected community sample, when compared to FAU.
2. *Parent Positive* will reduce the average levels of parent psychological distress, parental child-related stress and worries, family conflict and child emotional problems (secondary outcomes) in comparison to FAU.
3. The effects on the primary outcome will be greater where (i) children had higher baseline levels of conduct problems (i.e., more need for *Parent Positive*) and (ii) parents spent more time using the app.
4. *Parent Positive* will be cost-effective compared to FAU as a result of improved outcomes and cost savings.
5. **Trial design**

SPARKLE is a two-arm superiority parallel group RCT embedded in an existing large self-selected community cohort – Co-SPACE. Co-SPACE parents/carers (hereafter referred to as ‘parent’ for simplicity) aged ≥18 who have children aged 4-10 years will be invited to take part in the SPARKLE trial. Those who consent to SPARKLE will be randomised 1:1 to either *Parent Positive* or FAU. Outcome measures will be collected according to the Co-SPACE schedule at baseline (T1), which will be the Co-SPACE survey data obtained immediately prior to randomisation, and then at one month (T2) and two months (T3) post-randomisation. After completion of T3, parents will continue to be involved in Co-SPACE according to the Co-SPACE data collection schedule unless consent is withdrawn.

1. **Study setting**

SPARKLE will be embedded in Co-SPACE, a UK-wide longitudinal cohort study of mental health of parents, children and adolescents (4-16 years) during the COVID-19 pandemic (for more detailed information see Waite & Creswell, 2020, http://cospaceoxford.org/). The study started in March 2020 and has been tracking families every month using Qualtrics – an online data collection platform. From April 2021 to July 2021 an invitation to SPARKLE will be embedded in the Co-SPACE survey sent to parents of children aged 4-10 years.

1. **Inclusion & exclusion criteria**

First, the following Co-SPACE inclusion criteria will apply: parent is willing and able to give informed consent, must be at least 18 years old and lives in the UK. There are no exclusion criteria for Co-SPACE. Second, SPARKLE-specific criteria will be: parent has a child aged 4-10 years and has access to a smartphone with operating system OS 8-9 or higher (Android devices) or iOS 12-13 or higher (Apple devices). There will be no further exclusion criteria. Children will not be selected based on pre-existing conduct problems.

1. **Interventions**
   1. **Parent Positive:** This is an app developed for use on a smartphone providing a flexible digital space where parents can get support and advice to help them manage their children’s behaviour. It was developed by [name], [name], [name], [name], [name], [name] and [name] with digital design partner [TOAD](https://www.toadlondon.com/).

It consists of three zones:

1. The *Parenting Boosters* zone includes structured advice, support and tips for parents to deal with eight common parenting challenges. These are based around the series of [Families Under Pressure](https://familiesunderpressure.maudsleycharity.org/) animations identified and developed through co-design with parents. To increase their attractiveness and reach these were scripted to be light-hearted, humorous and non-judgmental and are delivered by eight high-profile British celebrities who are also parents. The eight messages relate to: (i) staying positive and motivated (Olivia Colman); (ii) making sure everyone knows what is expected of them (Sharon Horgan); (iii) building your child’s self-confidence and trust (Danny Dyer); (iv) getting your child to follow instructions (Rob Brydon); (v) promoting better behaviour (Jessica Ennis-Hill); (vi) limiting conflict (Holly Willoughby); (vii) keeping calm when your kids act up (Romesh Ranganathan); and (viii) careful use of sanctions (Shappi Khorsandi). In *Parent Positive,* the animations are supplemented by extended content to provide more information and advice for each challenge drawing on the [Empowering Parents, Empowering Communities](http://www.cpcs.org.uk/index.php?page=empowering-parents-empowering-communities) resources and the [STEPS](https://www.kcl.ac.uk/research/online-parent-training-for-the-initial-management-of-adhd-referral-optima) resources delivered in the form of videos, graphics and text – all based on over 20 years evidence from parent training studies (Daley et al. 2018).
2. The *Parenting Exchange* zone provides a facilitated parent-to-parent communication platform where parents are encouraged to raise any specific challenges they are facing to receive support from other parents. Trained parent facilitators will moderate the exchange and create posts to enhance engagement with the intervention. The Exchange will be also used to collate questions that parents have for experts (e.g., developmental psychologists, parent training practitioners, nutritionists, etc.) about a range of topics related to both the *Parent Positive* challenges and broader issues of direct relevance to children’s behaviour (e.g., sleep, diet, etc). These questions will be answered by experts at pre-recorded webinars held regularly during the period of the trial. The recording will be made available to parents using the app.
3. The *Parent Resources* zone will provide links to carefully selected high-quality, evidence-based online parenting resources reviewed and approved by a committee of parenting experts.

The app will be free and parents will be able to access the information when needed and in the order they choose. Parents in the intervention group will receive access during the immediate post-randomisation period until 30^th^ November 2021. To access the app, parents will receive an automated email with a link to download it from either Google Play (for Android users) or the App Store (for Apple users) together with brief instructions on how to download the app on the smartphone and register as a user.

- 1. **Follow-up as Usual (FAU):** FAU was selected as a comparator because the public health nature meant that an active comparator was not appropriate due to the pragmatic, rapid deployment of the trial. Individuals randomised to FAU will receive no intervention for the first 10 weeks while the data for baseline (T1), T2 and T3 are collected. They will then be given full access to the app until 30^th^ November 2021.
  2. **Criteria for discontinuing intervention.** We do not expect using *Parent Positive* to lead to harm that would suggest the intervention needs to be discontinued. However, parents will be able to withdraw from the trial at any point for any reason.
  3. **Strategies to increase engagement with the app and levels of app usage.** The traditional notion of adherence to an intervention protocol does not apply to public health intervention trials where samples are not restricted to those with a specific clinical need. This is the case in SPARKLE where we expect that a significant proportion of parents who are enrolled in the trial may not feel they need to use the app (i.e., those not having difficulties parenting their children’s behaviour). Nevertheless, we will initially encourage parents to use the app and promote high levels of engagement using push notifications on their mobile phone reminding them to engage with *Parent Positive*. Including the Parenting Exchange in the app is also expected to improve engagement. First, participants will be able to communicate with each other by posting and reading messages. Second, they will receive social feedback from their peers on their posts made within the Exchange. Third, they will be able to ask questions to experts via the Exchange.
  4. **Permitted concomitant care.** There will be no restrictions on concomitant care which will be monitored through collection of information on service use and harms.

1. **Measures and Outcomes**

[Co-SPACE](http://cospaceoxford.org/) routinely collects a wide range of measures. In this protocol we only describe those measures that will be included in the SPARKLE analysis. See Table 1 for the schedule of data collection for each measure. Where there are specific instructions for dealing with missing data for each measure, these will be followed. Where there are no specific instructions for missing data, we will prorate at the subscale level where there are 20% or fewer missing subscale items. For measures with no subscales, we will prorate at the overall scale level where there are 20% or fewer missing items overall.

- 1. **Child outcomes**
     1. **Conduct problems (T1 co-variate; primary outcome T2; secondary outcome T3; T1 moderator)**: This will be measured using the parent-rated conduct problems subscale of the Strengths and Difficulties Questionnaire (SDQ; Goodman, 1997). This is a widely used and validated five item subscale measuring oppositional, defiant and disruptive behaviour rated on a 3-point Likert scale (not true, somewhat true, and certainly true), with a mix of positive and negatively phrased items. Individual items’ scores are summed to derive an overall symptom subscale score. The level of ‘caseness’ at baseline will be presented for descriptive purposes. Data from this measure have been routinely collected from the Co-SPACE cohort every month.

Child conduct problems score was selected as the primary outcome because of the Co-SPACE finding reported above of a significant increase in average levels in the community since early on in the UK pandemic.

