**Figure 1. SPARKLE enrolment and group allocation procedure.**

1. **Sample**

A total of 616 will be recruited into the trial with 308 consenting parents randomised to each arm following SPARKLE baseline assessments. This sample size was powered to address our primary question whether comparing outcomes at one month post-randomisation, *Parent Positive* will reduce children’s conduct problems observed as compared to FAU. During the first UK lockdown (i.e., March to June 2020) there was around an approximate 0.2 standard deviation increase in SDQ conduct problems scores reported by Co-SPACE parents with children aged 4-10. For the current study, we took this as representing the smallest between group difference that was of clinical value to detect between *Parent Positive* and FAU scores post-randomisation (i.e., Cohen’s *d* of 0.2). We assumed a within trial drop-out rate of 30%, a correlation of 0.5 between one pre- and two post-randomisation measures (Machin, Campbell, Tan, & Tan, 2018), and using a one-tailed (Parent Positive > FAU) and an alpha of .05 that this number of participants provides 90% power to test the one-sided hypothesis that *Parent Positive* is superior to FAU.

1. **Recruitment**

Participants will be recruited into SPARKLE from the pool of Co-SPACE families of children aged 4-10. Recruitment into the Co-SPACE study is ongoing using advertisements on social media and through circulating information about the study to primary schools and relevant organisations, so SPARKLE may also recruit participants that are new to Co-SPACE.

1. **Allocation**

Participants will be enrolled into the study online via the Quatrics platform. Following consenting, simple randomisation will be carried out remotely within the Qualtrics programme using the Randomizer function, after which the parents in the *Parent Positive* group will be given access to the app as in section 7.4 above. Enrolled participants will be allocated to *Parent Positive* or FAU at the ratio of 1:1 by simple randomisation. Neither blocking nor stratification will be used.

1. **Blinding**

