Briefly, a mixed effects linear analysis of covariance (ANCOVA) model with repeated measures will be used with **the SDQ conduct problem** scores at one (primary outcome) and two months (secondary outcomes) post-randomisation as the dependent variables, and intervention group, time point, intervention group by time point interaction, baseline SDQ conduct problem score, gender and age of child as independent variables, with the interaction term used to extract the primary and secondary outcome effects at the two time points. Similar statistical models will be used to test for intervention effects on the other secondary outcome scale scores (average levels of parent psychological distress, parental child-related stress and worries, family conflict and child emotional problems) at one and two months post-randomisation. All analysis will follow the intention to treat (ITT) principle as far as possible (Sullivan et al., 2018; White et al., 2012).

**Aim iii) Are the effects of *Parent Positive* on the primary conduct problem outcome** **moderated by levels of (i) pre-existing levels of conduct problems (subgroup analysis) and (ii) *Parent Positive* usage levels as monitored during the one month intervention period (post-randomisation intervention** **effect modification analysis).**

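### The primary model adjusts for one baseline conduct score although earlier monthly scores on the same scale are already held; adding their mean is a cheap, conditional gain in a one-month test with about 77% power.

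*Protocol*

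**What the plan says.** - **Covariates.** Statistical analysis, Aims i and ii, names the adjustment terms of the repeated-measures model: "baseline SDQ conduct problem score, gender and age of child as independent variables". The effects at one and two months are extracted separately, and the one-month effect is primary.
- **Baseline.** Trial design defines T1 as the single Co-SPACE survey taken just before randomisation.
- **Earlier data.** Measures and Outcomes, Conduct problems, states: "Data from this measure have been routinely collected from the Co-SPACE cohort every month". Study setting says that the cohort began in March 2020 with monthly follow-up. SPARKLE recruits from April to July 2021.
- **Access.** Confidentiality links the SPARKLE ID to the Co-SPACE ID. Data management already has the junior statistician requesting Co-SPACE extracts for baseline.
- **Planning.** Sample states: "We assumed a within trial drop-out rate of 30%, a correlation of 0.5 between one pre- and two post-randomisation measures"; the test is set up "using a one-tailed (Parent Positive > FAU) and an alpha of .05"; and "this number of participants provides 90% power".
- **New joiners.** Recruitment allows that some participants may be new to Co-SPACE. They would have no earlier scores.

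**The concern.** A single five-item score is a noisy measure of a child's usual level of conduct problems. Scores from earlier months on the same child carry further information about that level, and they precede randomisation. For families already in the cohort they cost nothing to collect, but the planned model ignores them.

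This matters because the primary test has little precision to spare. The planned sample size rests on the variance of the average of two post-randomisation scores, whereas the primary effect is read at one month alone. At that time point power is well below the stated 90%. That mismatch is a separate matter, but it raises the value of any free precision.

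**Working it through.** **Inputs** (Protocol, Sample and Allocation): d = 0.2 with SD = 1, one-sided alpha 0.05, power 90%, correlation 0.5, 30% drop-out, one pre- and two post-randomisation measures, 308 per arm, 1:1.

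**Variance factor.** For v pre- and w post-randomisation scores with common correlation r:

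R = [1 + (w − 1)r]/w − v·r²/[1 + (v − 1)r]

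**Step 1: reproduce 616.** With v = 1, w = 2: R = 0.75 − 0.25 = 0.50. Then n per arm = 2(1.645 + 1.282)² × 0.50/0.2² = 214.1, rounded up to 215. Dividing by 0.7 gives 307.1, rounded up to 308, so the total is 616. The Protocol's figure is reproduced.

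**Step 2: the one-month test as planned.** With v = 1, w = 1: R = 1 − 0.25 = 0.75. Analysed per arm: 308 × 0.7 = 215.6. Power = Φ(0.2/√(2 × 0.75/215.6) − 1.645) = Φ(2.398 − 1.645) = 77.4%. With R = 0.50 the same formula gives 90.2%, so the loss is 12.8 points.

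**Step 3: add earlier scores, everyone has them, equal correlation 0.5** (w = 1):

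| Earlier scores besides T1 | R | One-sided power | N for 90% |
|---|---|---|---|
| 0 | 0.750 | 77.4% | 920 |
| 1 | 0.667 | 81.6% | 818 |
| 2 | 0.625 | 83.7% | 766 |
| 3 | 0.600 | 85.0% | 736 |

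The N in the first row is 322 per arm, 322/0.7 = 460, doubled. The others are 286, 268 and 257 per arm, divided by 0.7, rounded up and doubled. All exceed 616.

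**Step 4: only half have two earlier scores (assumption), mean fill plus missing indicator.** Where present, the mean of two earlier scores has variance (1 + 0.5)/2 = 0.75 and covariance 0.5 with both T1 and T2. After centring and filling, these become 0.375 and 0.25 over the whole sample. The variance explained by T1 and the filled mean is

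(0.5² × 0.375 − 2 × 0.5 × 0.25 × 0.25 + 0.25²)/(0.375 − 0.25²) = 0.09375/0.3125 = 0.30.

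So R = 0.70 and power = Φ(2.482 − 1.645) = 79.9%. This model forces one T1 slope on families with and without history. Adding an indicator-by-T1 term frees the slopes: R = (0.625 + 0.75)/2 = 0.6875, and power is 80.5%.

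**Step 5: correlation falls with time (assumptions), everyone has history.**

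- Fall of 0.03 per month (0.50, 0.47, 0.44, …): one, two, three and six earlier scores give R = 0.685, 0.662, 0.654 and 0.660, and power 80.6%, 81.8%, 82.2% and 81.9%.
- First-order autoregressive (0.5, 0.25, 0.125, …): given T1, earlier scores say nothing more about T2. R stays at 0.75 and power at 77.4%.

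With both the slow fall and only half having two earlier scores, the model of step 4 gives 79.2%.

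**The case against.** The strongest reply is that nothing here is an error. ANCOVA on one baseline score is valid and unbiased, and the Protocol is consistent about it: T1 is one survey, the planning assumes one pre-randomisation measure, and the model uses one. The model is also described only in brief, so the SAP may say more. This stands in part. The point concerns efficiency, not validity. But the Protocol does name its covariates, and it names one conduct score.

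A second reply is that the low power at one month comes from the sample-size calculation, which this change does not correct. That stands in full.

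A third is that the gain is uncertain. Monthly surveys of the cohort do not mean that each family answered monthly, and some participants may be new. A window of earlier months would also reach into different periods of restriction depending on entry date, which may weaken the longer-lag correlations. This stands too, and it is why the gain is given as a range.

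A reader might infer that earlier scores would recover most of the lost power. The documents do not support that. Two earlier scores recover about half of the 12.8 points (6.3) only if nearly everyone has them and correlation is flat. With half having them the recovery is about a fifth (2.5 points), and it can be nil. A reader might also infer that the same gain is available for every secondary scale. The Protocol states monthly collection explicitly only for the conduct scale.

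**Conclusion.** The point holds as a worthwhile, low-cost improvement to a valid model. At N = 616, d = 0.2, correlation 0.5 and one-sided 0.05, one-month power is 77.4% with T1 alone. Over the scenarios examined with up to three earlier scores it becomes anything from 77.4% (autoregressive) to 85.0% (three for everyone, flat correlation). With partial history or a slow fall in correlation, values of about 79% to 82% result.

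The flat-correlation case is not arbitrary: the Protocol's own calculation uses one value, 0.5, across its measures. But the share of families with history, the number of scores they hold and the correlations at longer lags are not in the documents. If the true correlation were 0.7 (an assumption), T1 alone would already give 89.7%, and two earlier scores for everyone 95.5%.

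The change does not restore 90% power on the planning assumptions. It does not replace reconciling the Sample section with the one-month primary analysis.

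**What to change.** Before any analysis by arm, pre-specify one added covariate in the primary model, besides T1: the mean of the same child's Co-SPACE SDQ conduct scores in a fixed window before T1. For parents with no score in the window, fill with the overall mean and include a missing indicator, optionally with an indicator-by-T1 term. Every randomised family then stays in the analysis. Because all these values precede randomisation, pre-specified adjustment for them does not bias the comparison.

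Choose the window after estimating, from existing Co-SPACE data, the correlations at lags beyond one month and the share of families with history. If correlation falls steeply, the sponsor can drop the idea at no loss. Extend it to a secondary scale only where earlier monthly scores are confirmed to exist.

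Cost: a slightly larger baseline extract, one or two degrees of freedom, and a few lines of model specification. New joiners contribute no gain.
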